# Comparison of D2 vs D3 lymph node dissection for RIght COloN cancer (RICON): study protocol for an international multicenter open-label randomized controlled trial

**DOI:** 10.1186/s13063-024-08269-5

**Published:** 2024-07-02

**Keywords:** Right colon cancer, D2 lymph node dissection, D3 lymph node dissection

## Abstract

**Background:**

Colon cancer is a global health concern, ranking fifth in both new diagnoses and deaths among tumors worldwide. Surgical intervention remains the primary treatment for localized cases, with a historical evolution marked by a focus on short-term outcomes. While Japan pioneered radical tumor removal with a systematic categorization of lymph nodes (D1, D2, D3), the dissemination of Japanese practices to the West was delayed until 90th of last century. Discrepancies between Japanese D3 dissection and the CME with CVL principle persist, with variations in longitudinal margins and recommended procedures. Non-randomized trials indicate the superiority of D3 over D2, but a consensus is lacking.

**Methods:**

This prospective, international, multicenter, randomized controlled trial employs a two-arm, parallel-group, open-label design to rigorously compare the 5-year overall survival outcomes between D2 and D3 lymph node dissection in stage II-III right colon cancer. Building on prior studies, the trial aims to address existing knowledge gaps and provide a comprehensive evaluation of the outcomes associated with D3 dissection. The study population comprises patients with right colon cancer, ensuring a focused investigation into the specific context of this disease. The trial design emphasizes its global scope and collaboration across multiple centers, enhancing the generalizability of the findings.

**Discussion:**

This study’s primary objective is to elucidate the potential superiority in 5-year overall survival benefits of D3 lymph node dissection compared to the conventional D2 approach in patients with stage II-III right colon cancer. By examining this specific subset of patients, the research aims to contribute valuable insights into optimizing surgical strategies for improved long-term outcomes. The trial’s international and multicenter nature enhances its applicability across diverse populations. The outcomes of this study may inform future guidelines and contribute to the ongoing discourse surrounding the standardization of colon cancer surgery, particularly in the context of right colon cancer.

**Trial registration:**

ClinicalTrials.gov NCT03200834. Registered on June 27, 2017.

**Supplementary Information:**

The online version contains supplementary material available at 10.1186/s13063-024-08269-5.

## Background and rationale

Colon cancer ranks 5th globally in both the number of newly diagnosed cases and the number of deaths among tumors in other locations [1]. The primary treatment method for patients with localized forms of colon cancer is surgery [2]. Lymphatic outflow from the right colon was described by Jamieson in 1909. In that study, regional lymph nodes were classified as paracolic, intermediate, and main nodes [3]. Nevertheless, the removal of all three levels of regional lymph nodes was not described in the literature as routine practice. Later, in Japan, questions regarding radical tumor removal began to emerge [4]. These questions primarily focused on the removal of the primary tumor and all regional lymph nodes, which were categorized into paracolic intermediate and apical nodes. Lymph node removal was classified as D1 (paracolic), D2 (paracolic and intermediate), and D3 (paracolic, intermediate, and apical). For stage II-III colon cancer, D3 lymph node dissection becoming mandatory [5].

However, it is worth noting that publications from Japan only became available to Western countries after 1990, leading to discussions in the West commencing in 2003 [6]. Subsequently, an article was published in 2009 regarding the standardization of colon cancer surgery [7], which introduced the abbreviation CME with CVL (complete mesocolic excision with central vascular ligation). Despite the prevalence of Japanese D3 lymph node dissection and the CME with CVL principle, there are certain differences [8]. Longitudinal margins with D3 lymph node dissection involve segmental resections of the colon depending on the feeding artery of the tumor, while an alternative method entails maintaining a 10-cm distance in the proximal and distal directions from the tumor. In the European approach, hemicolectomy or subtotal colectomy is recommended [6, 7]. The fundamental concept in D3 lymph node dissection is the removal of all regional lymph nodes, while in the CME with CVL concept, it involves sharp dissection with preservation of the mesocolic fascia and high ligation of the feeding vessels. The primary objective of both techniques is to enhance overall and disease-free survival. Numerous non-randomized controlled trials have demonstrated the superiority of D3 lymph node dissection over D2 in terms of overall and disease-free survival [9–12]. Other authors have shown comparable long-term results [13, 14]. Currently, the RELARC trial has investigated long-term outcomes (primary endpoint being 3-year disease-free survival) for right colon cancer, although the gold standard for treatment effectiveness remains 5-year overall survival [15]. In ins turn, COLD trial looked into 5-year overall survival between D2 and D3 lymph node dissection, but it included both right and left colon cancer as well as stage IV of the disease [16].

## Objectives

The aim of this study is to compare the 5-year overall survival between D2 and D3 lymph node dissection for right colon cancer in patients with stage II-III of the disease.

## Trial design

The study is an international, multicenter, two-arm, parallel-group, open-label, randomized controlled trial designed to ascertain whether D3 lymph node dissection confers a 5-year overall survival superior than D2 lymph node dissection (Fig. 1). We must address why there was a delay in submitting the study protocol. The primary reason stems from our initial uncertainties surrounding our ability to meet the large sample size requirement for recruitment, which posed a significant challenge for a single clinical center. In light of this, we expanded our network to include additional centers, thereby transitioning the study from a single-center to a multicenter trial.

**Fig. 1 Fig1:**
[figure not shown]
Flowchart of the study design

## Methods

### Study setting

Patients will be recruited from the Departments of Colorectal Cancer Surgery #1 and #2, as well as the Department of Laparoscopic and Minimally Invasive Surgery at the G.V. Bondar Republican Cancer Center in Donetsk, Ukraine. Additional recruitment locations include the Clinic of Coloproctology and Minimally Invasive Surgery at Sechenov University, Moscow City Oncology Hospital No. 62 in Moscow, Russia, and St. Luke’s Clinical Hospital in St. Petersburg, Russia (Fig. 2). All patients who meet the eligible criteria are proposed to be recruited in all centers. This study protocol is documented in accordance with the SPIRIT reporting guidelines [17]. The results of the trial will be reported in the subsequent publications.

**Fig. 2 Fig2:**
[figure not shown]
SPIRIT-figure

### Randomization and blinding

A simple 1:1 randomization was used in this study. A random number list was build using R studio software by an independent statistician and downloaded to electronic case report form (eCRF) with an allocation ratio 1:1 (D2 and D3 groups). After carefully selecting patients based on the inclusion and exclusion criteria, informed consent will be obtained by the corresponding investigators and the patients will be assigned to the corresponding intervention group. The trial is open-label, the surgeons are unblinded, and patients are clearly informed about the procedures they will undergo, as required by the healthcare systems of all centers in both countries. In the D2 lymph node dissection group, in case of intraoperative macroscopically suspicious apical lymph nodes are observed, the surgeon should remove them for ethical reasons. The patient will not be transferred to the D3 lymph node dissection group and will continue with follow-up as per the D2 group.

### Study population and eligible criteria

#### Inclusion criteria

Provision of signed informed consent by patientsConfirmation of adenocarcinoma of the right colon (cecum, ascending, hepatic flexure, and proximal transverse colon) verified by colonoscopyTumor staging as cT_3-4a,b_N_0_M_0_ (stage II) or cT_1-4a,b_N_1-2_M_0_ (stage III) on CTDemonstrated tolerability of chemotherapy drugsAge ranging from 18 to 75 yearsAmerican Society of Anesthesiologists (ASA) physical status classification of 1–3

#### Exclusion criteria

Presence of distant metastases (cM1)Tumor staging as cT_is_–cT_2_N_0_ (stage I) and cT4_b_ (involving the liver, kidney, head of the pancreas and duodenum, vena cava, aorta, or superior mesenteric vessels)Emergent cases (limited to tumor perforation and acute bowel obstruction)History of previous chemotherapy or radiation therapyPresence of synchronous or metachronous cancerPregnancy or breastfeedingRefusal to participate in trial

#### Withdrawal criteria

Exploratory laparotomy/laparoscopy or other reasons for refusing resection.

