### Definition of endpoints

#### OS and DFS

OS is the proportion of individuals in a study (in each group) who are alive 5 years after receiving the intervention. OS is defined by any-cause mortality.

DFS is the proportion of individuals in a study (in each group) who are alive 5 years after receiving the intervention, without experiencing local or distant recurrence or death from any cause. For DFS, an event is defined as local or distant recurrence or death. Participants who are lost to follow-up during the 5-year period post-procedure will be classified as censored. The survival analysis will be conducted using Kaplan–Meier curves, with comparisons made using the log-rank test.

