### Data analysis

Upon recruiting the last patient, a 5-year follow-up will commence. Intention-to-treat and per-protocol analysis will be conducted. Missing data will be imputed using Multivariate Imputation by Chained Equations (MICE package in R), except for survival data [25]. All collected data will be meticulously stored in the eCRF, and subsequent statistical analysis will be conducted. The data assessment process will be conducted in an anonymized manner, controlled by members of the university’s research group, who will solely handle the collected data. Data analysis will be solely conducted by the statisticians, also in an anonymized manner. The numeric variables will be presented as mean and standard deviation or median and range. For categorical variables, numbers and percentages will be expressed. *T*-test or Mann–Whitney *U* test will be employed for comparison between numeric variables, and chi-square or Fisher’s exact test will be used to compare categorical variables. A subgroup analysis by stage of the disease will be conducted. The survival analysis will be estimated using Kaplan–Meier curves, and comparisons will be made using the log-rank test. Cox regression will be applied to analyze the risk factors of survival. The event for overall survival will be defined as death from any cause, and for disease-free survival, it will be local or distant recurrence or death. Patients lost to the 5-year follow-up will be censored. All statistical tests are two-sided, and statistical significance is defined as *p* < 0.05. The statistical analysis will be performed in R Studio under the Affero General Public License version 3.

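### Withdrawing unresected patients after open-label assignment, and timing survival from receipt of surgery, leaves them no clear place in the promised intention-to-treat analysis

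*Protocol article*

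**What the plan says.** All references are to the protocol article.

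- **Randomization and blinding** puts assignment after eligibility and consent, before surgery: "informed consent will be obtained by the corresponding investigators and the patients will be assigned to the corresponding intervention group". It also states: "The trial is open-label, the surgeons are unblinded".
- **Withdrawal criteria** has a single entry: "Exploratory laparotomy/laparoscopy or other reasons for refusing resection".
- **OS and DFS** (under Definition of endpoints) fixes the origin of the primary endpoint: "OS is the proportion of individuals in a study (in each group) who are alive 5 years after receiving the intervention". DFS has the same origin.
- **Data analysis** states: "Intention-to-treat and per-protocol analysis will be conducted". It adds: "Patients lost to the 5-year follow-up will be censored". It does not say how a withdrawn patient is handled.
- For a different intraoperative event, removal of suspicious apical nodes in the D2 arm, **Randomization and blinding** does give a retention rule: "The patient will not be transferred to the D3 lymph node dissection group and will continue with follow-up as per the D2 group".

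**The concern.** Intention-to-treat means that everyone randomised is counted in the arm assigned, from a time point common to both arms. Here an event after randomisation, not being resected, leads to withdrawal, and the survival clock starts at a treatment that these patients do not receive. Two stated rules therefore pull against a third.

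The arm is known when resection is abandoned or refused, and the phrase covering other reasons is open-ended. If non-resection were commoner in one arm, leaving those patients out would compare groups that are no longer the randomised ones. Patients who have exploration only can be expected to do worse than resected patients, so the arm that lost more of them would look better than it is. With 34 deaths expected in total (24 in D2 and 10 in D3), a few uncounted deaths matter.

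**Working it through.** **1. The rules in sequence.** Take a patient who is randomised, explored and not resected.

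- Assignment has already happened (Randomization and blinding), so the patient belongs in an intention-to-treat set.
- Withdrawal criteria withdraws the patient, with no statement that survival follow-up continues. The apical-node rule shows that the article states retention explicitly in another situation.
- OS and DFS are counted from receiving the intervention. For a patient without resection that date is undefined, or at best ambiguous.
- If the patient stayed nominally in the set but follow-up ended at withdrawal, the censoring rule would remove them almost at time zero. They would contribute no events, so the effect would be much the same as exclusion.

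**2. The plan's own figures.** Sample size calculation gives 5-year OS of 75% (D2) and 90% (D3), 119 and 120 patients, and 24 + 10 = 34 deaths. A Lakatos log-rank calculation (two-sided 5%, 80% power, 3 years' accrual, 8 years in total, loss read as an annual hazard of 0.15) gives 239 to 244 patients, depending on the time grid, with about 25 and 10 deaths. The stated 239 is therefore reproduced on that reading of the loss. The present point does not turn on it.

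**3. Excess removal from one arm (illustration).** The documents give neither a non-resection rate nor the survival of unresected patients. Assume 10% 5-year survival in removed patients and n = 120. If S is the survival of all randomised patients in the arm and k are removed, the rest show

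(S − 0.10·k/120) / (1 − k/120)

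| S | k | Calculation | Result | Rise |
|---|---|---|---|---|
| 75% | 3 | 0.7475 / 0.975 | 76.7% | 1.7 points |
| 75% | 6 | 0.7450 / 0.950 | 78.4% | 3.4 points |
| 90% | 3 | 0.8975 / 0.975 | 92.1% | 2.1 points |
| 90% | 6 | 0.8950 / 0.950 | 94.2% | 4.2 points |

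Six such patients would account for 6 × 0.90 = 5.4 deaths, about 16% of the 34 expected.

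**4. Removal from both arms (illustration).** Now let 75% and 90% be survival among resected patients, let u be the unresected fraction and q their 5-year survival, varied from 0 to 30%. All-randomised survival in an arm is (1 − u)·R + u·q, where R is resected survival. A resected-only analysis shows 15.0 points in every row.

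| Unresected, D2 | Unresected, D3 | All-randomised difference |
|---|---|---|
| 2% | 2% | 14.7 |
| 5% | 5% | 14.3 |
| 2% | 5% | 12.0 to 12.9 |
| 2% | 8% | 9.3 to 11.1 |
| 5% | 2% | 16.1 to 17.0 |

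Example for 2% and 5% with q = 10%: D3 is 0.95 × 0.90 + 0.05 × 0.10 = 0.860, D2 is 0.98 × 0.75 + 0.02 × 0.10 = 0.737, and the difference is 12.3 points. These rows correspond to about 5 to 12 of the 239 patients. Balanced removal shifts the difference by under 1 point; unbalanced removal shifts it by about 1 to 6 points, in either direction.

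**5. No true difference among resected patients.** With 80% survival in both resected groups, a resected-only analysis shows 0. The all-randomised difference is −1.5 to −2.4 points for 2% against 5% unresected, and −3.0 to −4.8 points for 2% against 8%.

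**The case against.** The strongest reply is that nothing in the article says withdrawn patients leave the intention-to-treat set. Data analysis promises that analysis, and set definitions are commonly left to the full protocol or analysis plan, which are not shown. An exploratory operation also has a date that could serve as origin. This stands to the extent that exclusion is an inference. It does not remove the conflict, because the article itself states the withdrawal rule and the time origin, and neither fits the promised analysis as worded.

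A reader might infer several stronger claims that the documents do not support:

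- **That the unblinded surgeon drops the worst-prognosis patients.** Other reasons for refusing resection may include the patient's own refusal, and such patients need not have a poor prognosis.
- **That D3 will lose more patients because it works along the superior mesenteric vein.** The D3 field does expose structures that D2 leaves unseen. But nothing says that difficulty there leads to abandoning resection, and the exclusion criteria already remove T4b tumours involving the superior mesenteric vessels, pancreatic head or duodenum at clinical staging. A differential is possible but not shown.
- **That a per-protocol set would discard D2 patients whose suspicious apical nodes were removed.** The protocol prescribes that removal and keeps these patients in D2, so it is adherence. No per-protocol set treating them as deviators is described.
- **That listing intention-to-treat and per-protocol together allows two primary answers.** Naming the primary set is ordinary content of an analysis plan, and its absence here is not a finding.

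**Conclusion.** The point holds as an unresolved conflict in stated rules. Randomised but unresected patients have no clear origin for OS and DFS and no stated follow-up, and they may be missing from the intention-to-treat analysis. Because the arm is known when resection is abandoned, unequal removal could bias the primary comparison.

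The size and direction of any bias cannot be derived from the documents. The 1.7 to 4.2 points rest on two assumptions: 10% survival in removed patients, and an excess of 3 to 6 removals in one arm. If removal is balanced, the effect on the difference is small. The case for acting is that the rules decide who is counted in the primary comparison and that correction is cheap, not that bias has been demonstrated.

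**What to change.** 1. Time OS and DFS from the date of randomisation.
2. Define the intention-to-treat set as all randomised patients in their allocated arm, with no exclusion for findings at exploration. Limiting it to eligible patients could bring the exclusion back, since those found to have more advanced disease at surgery could be relabelled ineligible.
3. Reword the withdrawal criterion as not receiving the allocated surgery, with survival follow-up continued.
4. Retrieve vital status for anyone already withdrawn.
5. Report non-resection by arm and reason.
6. Confine any resected-only analysis to a per-protocol sensitivity analysis.

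**Cost.** The changes are to wording, with a little data retrieval. DFS needs a rule for patients who are never resected, for example an event at randomisation. The effect is slightly diluted if the planning figures of 75% and 90% were meant for resected patients: with 2% unresected in both arms the difference is 14.7 points and power is 76 to 78%, and with 5% it is 14.3 points and 70 to 72% (two-proportion test, 102 evaluable per arm = 120 × 0.85). Recruitment ended on 11 September 2023 and 5-year follow-up runs from the last patient, so there is time to act, but retrieval becomes harder with delay.

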#### Criteria for study centers and intervention performers

The hospital must specialize in colorectal cancer surgery.Surgeons involved in the study should have experience in conducting a minimum of 50 elective colon cancer resections.They must demonstrate a commitment to fully complying with the protocol requirements of this study.

### Interventions

#### Informed consent

Doctors will present the trial to patients and provide them with information cards. They will then discuss the details of the trial as outlined on the cards with the patients. Following these discussions, doctors will seek written consent from patients who agree to participate in the trial.

#### Laboratory research

Complete blood count (CBC) and urine testsBiochemical blood tests (urea, creatinine, bilirubin, blood sugar, ALT, AST, α-amylase, total protein)CoagulogramTumor markers: CEA, CA19-9

#### Instrumental studies

Colonoscopy with biopsy for diagnosis verificationComputed tomography of the abdominal and thoracic cavity with intravenous bolus contrastEsophagogastroduodenoscopyElectrocardiogram, echocardiography if necessary

#### Surgery

The surgical procedures encompass two types: right hemicolectomy and extended right hemicolectomy. The distinction lies in the level of middle colic artery ligation and the removal of different portions of the transverse colon. In right hemicolectomy, only the right branch of the middle colic artery is transected, along with division of the proximal transverse colon. Extended right hemicolectomy involves ligation of the middle colic artery at its origin and transection of the mid transverse colon.

#### Techniques for the right *colon* mobilization

The surgical technique for the right colon mobilization includes four steps: cranial, caudal, medial, and lateral. The cranial approach initiates from entry into the lesser sac and continues distally to the level of ileocolic pedicle. The caudal mobilization starts from the embryonic plane under the ileum and progresses proximally to the level of the Henle’s trunk. The medial approach involves movement into the embryonic plane beneath the ileocolic artery and continues in the proximal, distal, and lateral directions to the levels of transverse colon and ileum transection. Lateral approach is carried out by dissecting Toldt’s line between the mesocolic fascia and Gerota’s fascia, continuing until the level of superior mesenteric vessels. Full-length mobilization includes the preservation of mesocolic fascia, except the cases of locally advanced cancer, where excision beyond the embryological planes is required.

#### The boundaries of D2 and D3 lymph node dissection

The proximal boundary of D2 lymph node dissection is defined by the location of mesocolon fixation to the Gerota’s fascia and the descending duodenum. In D3 lymph node dissection, the additional boundary extends to the head of the pancreas, up to the gastroepiploic vein and the lower edge of the pancreatic neck.

The distal boundary for D2 lymph node dissection starts from the ileum, 10 cm from the cecum, continuing 1 cm below the projection of ileocolic vessels until 1 cm laterally from the superior mesenteric vein (SMV). For D3 lymph node dissection, the distal resection margin additionally includes the opening of the anterior surface of the SMV, 1 cm below the origin of ileocolic vein. Paracolic lymph nodes should be removed at a minimum distance of 10 cm from the tumor in both the proximal and distal direction.

The lateral border for D2 and D3 lymph node dissection is defined by the white line of Toldt.

The surgical trunk (medial boundary) for D2 lymph node dissection is set at 1 cm from the lateral edge of the SMV at the level of the ileocolic artery and vein, extending proximally to the anterior surface of the duodenum. The head of the pancreas and origin of the feeding arteries are not visualized, along with the superior mesenteric vein and Henle’s trunk.

The surgical trunk (medial boundary) for D3 lymph node dissection is the medial side of the SMV from the lower border of the pancreatic neck to 1 cm below the origin of the ileocolic vein (Figs. 3, 4, 5, and 6). The anterior surface of the SMV, origin of the feeding vessels, and ligation of the intestinal tributary of Henle’s trunk serve as anatomical landmarks of complete D3 lymph node dissection. When the ileocolic artery and/or right colic artery pass behind the SMV, the ligation of these arteries is carried out at the lateral side of the SMV.

